**Information collected within the first 24 hours of inpatient stay**			
	Inpatient stay patient flow	Inpatient movement	ICU or HDU admission, ward class, duration of ICU or HDU stay, hospital departments, surgeries
	Inpatient vital	Inpatient vital signs	Pulse, respiration, SpO_2_, systolic BP, diastolic BP, temperature, Glasgow coma scale, height, weight, BMI
	Inpatient laboratory	Inpatient laboratory	Laboratory measurement frequency and major laboratory test results: albumin, potassium, creatinine, sodium, bicarbonate, creatine kinase, creatine kinase_MB (mass), C-reactive protein, prothrombin time, procalcitonin, blood PH, glycated hemoglobin A1c, triglycerides, cholesterol, high-density lipoprotein cholesterol, low-density lipoprotein cholesterol
	Inpatient treatment	Inpatient treatment and order	Major medication prescription and order
**Information collected at discharge**			
	Health care utilization summary	Inpatient movement	Count of ED visits, ED admissions, surgeries, ICU or HDU admissions last year
	Discharge information	Discharge diagnosis	Primary discharge diagnosis, discharge location, length of stay
	Outcomes	Inpatient movement, discharge diagnosis	ICU transfer, inpatient mortality, cardiac arrest, prolonged hospital length of stay
**Information collected after discharge**			
	Outcomes	ED root table	2/7/30-day mortality, emergency readmission, ED revisit

^a^ED: emergency department.

^b^ICU: intensive care unit.

^c^HDU: high dependency unit.

^d^SpO_2_: peripheral oxygen saturation.

^e^BP: blood pressure.

### Predictive Modelling for Clinical Decision Making

In this study, we will develop and validate a novel interpretable triage system for risk stratification of patients in the ED. Our proposed solution will be compared with baseline risk prediction tools such as traditional clinical scores and black box machine learning models. The extracted data set will be split into training, validation, and testing sets to build and validate the predictive models. The ED visit episodes from January 1, 2008, to December 31, 2018, will be randomly divided into 2 non-overlapping cohorts: a training cohort (80%) and a validation cohort (20%). The ED visits dated in 2019 are assigned to one testing cohort, while those dated in 2020 are assigned to a second testing cohort covering the period of the COVID-19 pandemic [40,41]. Using this sequential testing design, we will be able to test whether the population shift and the COVID-19 pandemic would impact model performance [42]. Further details are presented below.

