### Study Cohort and Design

The flowchart of the entire project is shown in Figure 1. In the extracted data set, there are 3 primary identifiers: “*ED Case No,” “Admission Case No,”* and “*Patient ID,”* to represent the unique ED visit, the admission case, and the patient, respectively. Figure 2 illustrates how variables are constructed from and linked to these 3 identifiers. By consolidating the selected variables, a master data set will be created. Afterwards, the constructed master data set will be processed with outlier removal and missing value handling. The interpretable machine learning framework will then be implemented, and the models will be evaluated and compared with other baseline approaches, including traditional clinical scores, machine learning, and deep learning.

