### Data Source and Extraction

Study subjects have been drawn from the hospital’s EHRs using the SingHealth-IHiS Electronic Health Intelligence System, which combines data from multiple clinical, operational, and finance data sources [33]. Before analysis, all data, including the 3 primary identifiers, have been de-identified to ensure that they are sufficiently anonymous. Records of deaths are obtained from the national death registry and are matched to specific patients in our database. Relevant variables are extracted from the beginning of the ED visits until the end of the patient’s journey. Moreover, patients’ medical histories are extracted and matched for each unique patient through *“Patient ID.”* The extracted data were saved in multiple CSV files for subsequent processing and analysis.

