The clinical risk-scoring models have been traditionally developed in 2 ways: through expert opinions or consensus and conventional cohort studies. However, both approaches are labor-intensive and are not easy to update over time. Recently, we developed an interpretable machine learning–based automatic clinical score generator, AutoScore, as a practical and universal solution for risk scoring [29]. Using the AutoScore framework, users could seamlessly generate parsimonious risk models (ie, point-based sparse risk scores), thereby supporting automated machine learning solutions in health care [43]. AutoScore comprises 6 modules. In module 1, random forest is used to rank variables in terms of their contribution to modelling. Module 2 categorizes continuous variables to address nonlinearity and facilitate the generation of point-based scores. Module 3 computes scores based on a subset of variables and logistic regression, while module 4 determines the optimal number of variables based on a parsimony plot. Module 5 enables fine-tuning of the cut-off values for categorizing continuous variables for preferable interpretation, and module 6 provides a final performance evaluation. AutoScore is used to develop the 3 SERT scoring algorithms with the candidate variables and the outcomes.

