### Model Comparison and Performance Metrics

To evaluate the performance of all predictive models, receiver operating characteristic (ROC) analysis will be conducted on the 2 testing cohorts. An overall measure of predictive performance is represented by the area under the ROC curve. Moreover, we will calculate the measures of diagnostic accuracy, such as sensitivity, specificity, positive predictive value, and negative predictive value. These specific measures are determined by setting thresholds on each ROC curve. To achieve optimal balance between sensitivity and specificity, we will select the cut-off points closest to the plot area’s upper-left corner. The 95% CIs for each model or score will also be reported and compared.

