## Results

The raw data have been extracted, and we are currently linking and cleaning the data. In the data extraction process, we included all patients who visited the ED at Singapore General Hospital between January 1, 2008, and December 31, 2020. Patients under the age of 21 years were excluded. If the patients were admitted through the corresponding ED visit, they would be followed throughout their inpatient stay. The data set contains more than 1.8 million ED visit episodes of over 810,000 unique patients. Approximately 650,000 of these ED visits resulted in subsequent hospitalizations. Our findings and modelling results are expected to be published by 2022.

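### The 2008–2018 data are split by ED visit rather than by patient, so the validation cohort is not independent of the training cohort (low severity)

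*Protocol article*

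**What the plan says.** The section Predictive Modelling for Clinical Decision Making names the unit of the random split: "The ED visit episodes from January 1, 2008, to December 31, 2018, will be randomly divided into 2 non-overlapping cohorts". Training receives 80% and validation 20%. Visits in 2019 and in 2020 form two separate testing cohorts.

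The section Study Cohort and Design lists three identifiers (ED Case No, Admission Case No, Patient ID), which serve "to represent the unique ED visit, the admission case, and the patient, respectively". The section Data Source and Extraction adds that "patients’ medical histories are extracted and matched for each unique patient through" Patient ID. A patient key therefore exists and is already used for linkage. The article nowhere says that all visits of one patient are kept in the same cohort.

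The Results section gives the scale: "The data set contains more than 1.8 million ED visit episodes of over 810,000 unique patients". The extraction covers visits "between January 1, 2008, and December 31, 2020".

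On model building, the section on the proposed method says that in AutoScore "module 4 determines the optimal number of variables based on a parsimony plot". It does not say which cohort the plot is drawn from. On evaluation, the section Model Comparison and Performance Metrics says that "receiver operating characteristic (ROC) analysis will be conducted on the 2 testing cohorts".

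**The concern.** A validation cohort is useful for choosing between models only if it is independent of the data used to fit them. When visits are randomised, a patient with several visits will often have some in each cohort.

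Such visits are not independent. They share demographics and postal code, largely the same comorbidity indices, and overlapping counts of past use (Table 1). For 30-day mortality, which SERT-3 predicts, two admissions shortly before one death can both be labelled positive by that death, one in training and the other in validation.

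At stake is any choice made on the validation cohort. A model that partly recognises individual patients will look better there than it would on new patients. Flexible learners can exploit this more than a short point score can. If the number of variables or the network settings are chosen on such data, the choice may lean towards more complexity than is warranted.

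**Working it through.** The article states no overlap figure, so there is none to reproduce. The check asks what share of validation visits come from a patient who also has a visit in training.

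**Inputs from the article**
- Visits, 2008–2020: 1.8 million (given as more than this).
- Unique patients, 2008–2020: 810,000 (given as over this).
- Mean visits per patient: 1,800,000 / 810,000 = 2.22.
- Validation fraction: 0.2.

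The rounded counts are treated as exact.

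**Formula.** Take a validation visit of a patient with k visits. All k − 1 other visits fall in validation with probability 0.2^(k−1), so at least one is in training with probability 1 − 0.2^(k−1). With n_k patients having k visits, the visit-weighted share is

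1 − Σ n_k · k · 0.2^(k−1) / Σ n_k · k.

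**Lower bound without a distribution.** The term k · 0.2^(k−1) equals 1, 0.4, 0.12 for k = 1, 2, 3 and keeps falling, so it never exceeds 1. The numerator is therefore at most the number of patients, and

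share ≥ 1 − patients / visits = 1 − 810,000 / 1,800,000 = 55%.

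**Narrowing to 2008–2018.** The split uses 11 of the 13 years, and the article gives no counts for that window. Assuming even volume, visits are 1,800,000 × 11/13 ≈ 1,523,000, of which 20% ≈ 305,000 are in validation. The visit-count distributions below are assumptions. Each has mean 2.22 over 13 years, with each visit kept with probability 11/13 for the second column.

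| Assumed distribution | Share, 13 years | Share, 2008–2018 |
|---|---|---|
| Zero-truncated Poisson | 78% | 72% |
| Geometric | 74% | 70% |
| Log-series | 72% | 68% |
| Zipf, at most 300 visits | 65% | 63% |
| 1 or 20 visits | 58% | 58% |
| 1 or 100 visits | 56% | 56% |

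The geometric 13-year value can be done by hand. With p = 1/2.22 = 0.45, the share is 1 − (0.45 / (1 − 0.2 × 0.55))² = 1 − (0.45 / 0.89)² = 74.4%. A Monte Carlo run of the geometric case for 2008–2018 gave 69.9%.

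**Worst case for 2008–2018.** Suppose all 810,000 patients appeared in those 11 years and almost no one accounted for all the repeat visits. The bound is then 1 − 810,000 / 1,523,000 ≈ 47% (46–48% for 1.50 to 1.56 million visits). It rises above 50% once the patients seen in 2008–2018 number fewer than 1,523,000 / 2 ≈ 762,000, which is 94% of 810,000.

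**After the change.** Splitting the same simulated data on Patient ID gave 0% overlap, with 20.0% of visits in validation.

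**The case against.** The strongest reply is that nothing the article plans to report is shown to be wrong.

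- **Reported performance lies elsewhere.** ROC analysis is placed on the 2019 and 2020 cohorts, which are set by calendar year and are not part of the random split. A reader might infer that the headline AUCs are inflated, but the article does not support that. This stands.
- **Tuning is largely not on the validation cohort.** A reader might infer that variables, cut-offs and hyperparameters are all chosen there. The article presets the random forest settings from earlier literature and tunes the LASSO by 10-fold cross-validation. It describes cut-off adjustment as serving interpretation and names no cohort for it or for the parsimony plot. What plausibly remains is the parsimony plot and the tuning of the LSTM/MLP network. This stands, and it narrows the point.
- **The word non-overlapping is not false.** Its subject is visit episodes, and those are disjoint. The article makes no patient-level claim, so it does not contradict itself. This stands.
- **The optimism may be negligible for the product of the study.** A sparse point score fitted to about 1.2 million training visits (80% of 1,523,000) has little capacity to memorise patients. The article gives no between-patient variance and no event rate for most outcomes. Any AUC inflation figure would therefore reflect the assumptions of whoever simulated it, and none is claimed here. This stands too.
- **Shared deaths are limited.** The mortality outcomes concern admitted patients, and SERT-1 and SERT-2 use 2-day or 2- and 7-day horizons. The shared-death argument bears mainly on the 30-day outcome of SERT-3.

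The reply does not remove the dependence itself. The article fixes the visit as the unit, has a patient identifier to hand and gives no grouping rule. A later test cohort measures the model that was chosen. It does not revisit a choice made on dependent data.

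**Conclusion.** The concern holds in a limited form. The cohorts are disjoint by visit but not by patient. At least 55% of validation visits at the full-data ratio share a patient with training, and about 56–72% do so in 2008–2018. The first figure needs only the article's two counts. The second also assumes even annual volume and one of the visit distributions listed. Only an implausible extreme falls just below half. These shares count visits. Counted by patient, the overlap in 2008–2018 depends much more on the distribution, from 7% to 72% across the same cases.

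Validation results, and any selection made on them, are therefore not independent of training and may be optimistic, more so for the flexible models. The size is unknown and is probably small for the SERT point scores. The ROC results on the 2019 and 2020 cohorts are not shown to be biased by this split. Severity is low.

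**What to change.** Randomise the 2008–2018 data on Patient ID, with 80% of patients in training and 20% in validation, so that all visits of a patient in those years fall in one cohort. Form the 10 LASSO cross-validation folds by patient as well. State in the section Predictive Modelling for Clinical Decision Making that the two cohorts are disjoint by patient.

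The cost is small. The identifier already exists, no data are lost, and linking and cleaning were still under way when the article was written. The one drawback is that the visit ratio will be only approximately 80:20.

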### Strengths

First, this study uses a large set of EHR data over a 13-year period, which contains comprehensive patient information. As Singapore’s largest hospital, Singapore General Hospital provides medical care to a wide range of patients throughout the country; thus, its EHRs ensure good coverage for a large population. Additionally, the longitudinal data allow us to validate the SERT system using data before and after COVID-19. Thus, we will have the opportunity to evaluate the impact of the global pandemic on triage performance in the ED. The insights gained from system evaluation could be used to examine possible model adaptations in shifted clinical settings.

Second, the SERT triaging system we intend to develop will be transparent and easily understandable. All 3 SERT scores are parsimonious and point-based, as only the most significant variables are considered in their formulation. Their formats follow the same convention as widely used clinical scores such as the National Early Warning Score and Modified Early Warning Score, allowing for easy comprehension and quick adoption. In contrast, black box machine learning models are challenging to comprehend, making them inaccessible to clinicians [25]. Although there are techniques for post hoc model explanation, most machine learning models are not inherently interpretable [25].

Third, this project aims to develop a dynamic system capable of identifying risk strata at different decision points in the ED. During the initial triage process and the patient’s stay in the ED, SERT predicts the likelihood of inpatient and ICU admissions. Whenever variables are altered, the scores can be updated, making the risk assessment dynamic and practical. In addition, SERT can make mortality predictions to assess the likelihood of the worst outcomes for patients who will be hospitalized.

Lastly, the simple form of the scores in SERT permits a variety of implementation schemes. As an example, the actual implementation can be as simple as a mobile app. Users may input relevant information into the app, which will return a risk score at the time of inquiry. The SERT scoring platform can also be easily integrated into existing information technology systems, which requires only simple calculations and therefore little computing power. The application can be designed and implemented in real time, similar to that seen in a recent study in the United States [13].

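### The single 2019-to-2020 contrast cannot separate a pandemic effect from one more year of ordinary drift, although the article says the pandemic's impact can be tested

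*Protocol article*

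**What the plan says.** Under Predictive Modelling for Clinical Decision Making, the protocol article fixes the time structure. "The ED visit episodes from January 1, 2008, to December 31, 2018, will be randomly divided into 2 non-overlapping cohorts", 80% for training and 20% for validation. Then: "The ED visits dated in 2019 are assigned to one testing cohort, while those dated in 2020 are assigned to a second testing cohort", the latter described as "second testing cohort covering the period of the COVID-19 pandemic". The same section draws the inference: "Using this sequential testing design, we will be able to test whether the population shift and the COVID-19 pandemic would impact model performance".

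Model Comparison and Performance Metrics plans ROC analysis on the two testing cohorts, with 95% confidence intervals for each model or score. Results gives the extraction window as "between January 1, 2008, and December 31, 2020".

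Strengths goes further. It states that "the longitudinal data allow us to validate the SERT system using data before and after COVID-19" and that "we will have the opportunity to evaluate the impact of the global pandemic on triage performance in the ED". It adds that what is learned could guide adaptation of the models to changed clinical settings.

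**The concern.** A score fitted to past data usually loses or changes performance as patients, coding and practice move on. Training stops at the end of 2018, so the 2019 cohort covers the first year beyond training and the 2020 cohort the second. The pandemic cohort and the second-year cohort are the same visits. A fall, or a rise, from 2019 to 2020 could come from ageing of the score, from the pandemic, or from both in either direction.

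What is at stake is the interpretation that the article lists as a strength. Ordinary ageing points to routine updating of a score; a pandemic effect points to a different response. If the two cannot be told apart, the 2020 result cannot guide that choice. Drift in the opposite direction could also hide a real pandemic effect.

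**Working it through.** **1. The plan's own figure.** Strengths gives a 13-year data period: 2020 − 2008 + 1 = 13. It reproduces.

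**2. Distance from training.** Training and validation end on December 31, 2018. The midpoints of the 2019 and 2020 cohorts lie 0.50 and 1.50 years after that date, and 6.0 and 7.0 years after the midpoint of 2008-2018. On either measure, 2020 is one year further out.

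**3. What the contrast estimates.** Let g be the change in AUC from one more year of ordinary drift, c the pandemic effect on AUC, and f the share of 2020 visits before pandemic conditions began. To a first approximation,

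AUC(2020) − AUC(2019) = g + (1 − f)c.

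This is one equation in two unknowns even if f is known. For example, with f = 0, a drift of −0.01 with no pandemic effect and a pandemic effect of −0.01 with no drift both give −0.01.

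The random 20% validation sample does not supply g. It mixes 11 years (2008-2018) with the training data and is used in model building, so the step from validation to 2019 is not a clean one-year drift.

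**4. Size for the admission outcome.** The documents state neither an AUC nor a drift rate; both are assumed. Hanley-McNeil, with n1 events and n0 non-events:

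SE² = [A(1−A) + (n1−1)(Q1−A²) + (n0−1)(Q2−A²)] / (n1·n0), Q1 = A/(2−A), Q2 = 2A²/(1+A).

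With A = 0.80: Q1 − A² = 0.0267 and Q2 − A² = 0.0711.

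- Study Setting figures (120,000 visits and 36,000 admitted per year, so 84,000 not admitted): SE² = 6,933 / 3.024×10⁹, SE = 0.0015. The difference of two years has SE 0.0015 × √2 = 0.0021.
- Averages from Results (1.8 million / 13 ≈ 138,000 visits; 650,000 / 13 = 50,000 admitted): SE = 0.0013; difference 0.0019.

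With c = 0, drift alone gives a difference that is significant at the two-sided 5% level with these probabilities:

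| Basis | Drift 0.005 | Drift 0.01 |
|---|---|---|
| 36,000 of 120,000 | z = 2.3, 0.65 | z = 4.7, about 1.00 |
| 50,000 of 138,000 | z = 2.7, 0.77 | z = 5.4, about 1.00 |

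**5. Size for rare outcomes.** Take 50,000 admitted patients a year and an event rate of 1% or 5% (assumed), again with A = 0.80. The SE of the difference is 0.0169 or 0.0076. Drift of 0.005 to 0.01 alone is significant with probability 0.06 to 0.09 at 1%, and 0.10 to 0.26 at 5%.

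These SEs treat the two years as independent and assume that 2020 had an average volume. The article gives no count for 2020, and some patients appear in both years.

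**6. Dilution.** The article gives no onset date. If 0 to 16 weeks of 2020 were pre-pandemic (assumed range) and visits were spread evenly, f = 0 to 112/366 = 0.31. The cohort would then show between 100% and 69% of a true pandemic effect.

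**The case against.** The strongest reply is that the article is more careful than the concern suggests. It names population shift next to COVID-19, and it holds out 2019 as a pre-pandemic year, so drift is partly anticipated. A reader might infer that the plan attributes the whole 2020 change to COVID-19. The documents do not support that: no such rule is stated. Nor is a significance test of 2019 against 2020 described, so the probabilities above show how easily drift could look like an effect, not what will be reported. This stands, and it limits the point to inseparability. Naming two causes does not separate them when there is one contrast, and Strengths then names the pandemic alone.

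A reader might also infer that the data contain nothing after COVID-19. That holds only if after means after the pandemic ended. Read as after its onset, 2020 supplies such data, so the wording is ambiguous rather than false. The presence of pre-pandemic weeks is likewise plausible but not documented.

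It can also be said that even trivial drift would not be clear for every outcome. That is right: the admission figures do not carry over to rare outcomes.

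Finally, a condensed article may leave an onset date or period analysis to a fuller document. That excuses the missing date. It does not excuse the stated cohort boundaries combined with the stated inference.

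**Conclusion.** The point holds as a limit on interpretation. Followed exactly, the plan leaves pandemic effect and time since training fully confounded, while the article says the pandemic's impact can be tested. The confounding follows from the cohort dates alone and needs no assumption.

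Its size does need assumptions. For admission, at an AUC of 0.80, drift of 0.005 per year alone would be significant with probability about 0.65 to 0.77. For outcomes at 1-5% of admitted patients, with drift of 0.005 to 0.01, the range is about 0.06 to 0.26. Dilution of a real effect could reach about 31% if 16 weeks of 2020 were pre-pandemic.

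Development of the three SERT scores, their comparison with other tools, and separate reporting of performance in 2019 and 2020 are not affected. The change should be made because the claim is presented as a strength and can be repaired with data already in hand.

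**What to change.** Add a lag-matched control. Rerun the same pipeline on 2008-2017, test it on 2019, and compare that result with the 2008-2018 score tested on 2020. Both tests then fall in the second year after training. State the assumption that two-year drift is similar in the two periods, and note that the control has 10 training years instead of 11 and may select different variables or cut-offs.

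Split 2020 at a prespecified local onset date and compare the pandemic months with the same calendar months of 2019, so that season stays balanced.

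If this is not done, limit the statements in Predictive Modelling for Clinical Decision Making and in Strengths to performance in 2020, without attributing a change to COVID-19. In either case, describe the data as before and during COVID-19.

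The cost is extra model runs for each SERT score and outcome, including the cut-off tuning, and a smaller 2020 pandemic subset with wider intervals, which matters most for rare outcomes. No new data are needed. The wording changes alone cost nothing.
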